### 5.4.2 Phase I – part

The optimum dosage of BIBF 1120 in combination with low-dose cytarabine will be determined in a phase I part. Based on acceptable safety data for BIBF 1120 monotherapy, there will be a rapid dose finding. Dose finding will proceed in a classical 3+3-design. Predefined dose levels are: 100mg (dose level 1), 150mg, (dose level 2), and 200mg (dose level 3) twice daily. A cohort of three patients will be treated in each dose level and toxicity will be assessed in the first treatment cycle (28 days) by Common Terminology Criteria for Adverse Events V 4.0 (CTCAE). Patients evaluable for this safety analysis have to have received at least one dose of BIBF1120 and AraC. In case of no dose limiting toxicity (DLT), the dose will be increased by one dose level. In case of one DLT, up to three further patients will be recruited into the same dose level. If >1 DLT occurs in one dose level in up to six patients, this dose level will not be further evaluated. The highest dose level with  $\leq 1$  DLT out of six patients will be defined as the maximum tolerable dose (MTD) and will be evaluated in the phase II part of the study after approval of the data monitoring committee (DMC). Dose levels considered for phase II with less than six patients evaluated (i.e. no DLT in three patients) will further recruit patients until a total of six evaluable patients and will be chosen for phase II only if the aforementioned condition ( $\leq 1$  DLT out of six patients) applies. In case of >1 DLT in the dose level 1 cohort, the dose will be decreased to dose level 0 (100 mg BIBF 1120 once daily). The study will not proceed to the phase II part if >1 DLT occurs in dose level 0. A DLT is defined as every severe adverse reaction CTC grade IV with possible or definite relationship to the study drug BIBF1120. Therapy-related cytopenias as signs of an intended antileukemic activity do not fulfill the definition of an adverse events and therefore cannot constitute an SAE or DLT. The following known, frequent and often inevitable complications from therapy-related cytopenias are also excluded from DLT: neutropenic fever, neutropenic infections and thrombocytopenic bleedings. Notwithstanding, these complications may constitute a DLT if occurring in an unexpected high frequency, as judged by the DMC, and should be reported as an AE or SAE as appropriate (see 7). Complications attributable to disease progression in the judgement of the investigator are also excluded from DLT. These include:

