
- neutropenic infections due to disease progression\*
- thrombocytopenic bleedings due to disease progression\*
- deterioration of the general condition due to leukemia progression\*
- laboratory abnormalities due to leukemia progression\*
- death due to disease progression\*

- tumor lysis syndrome due to disease progression\*
- organ failure (i.e. renal insufficiency, coagulopathy, respiratory failure, hypotension) due to disease progression\*

\*leukemia progression defined as at least one of the following: reappearance of blasts in the peripheral blood, raising blast counts in the peripheral blood, raising blast counts in bone marrow, appearance, reappearance or progression of chloromas, raising lactate dehydrogenase serum level with no other explanation)

Patients responding after the therapy (CR, CRp, CRi) or with progressive disease or intolerable toxicity will be observed until 28 days after the last application of study medication. Patients with a partial remission or stable disease will continue in protocol treatment for up to six therapy cycles.

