## 9 QUALITY ASSURANCE

### 9.1 Data Monitoring Committee

The DMC will monitor the safety of the study. During phase I, the DMC members will receive safety reports after completion of each dose level. In addition, the DMC decides on the recommended dose for phase II before start of phase II of the study. During the phase II part of the study, the DMC members will receive safety reports every 3 months. After receipt of each safety report the DMC can recommend about continuation, modification, or termination of the study. For details of the DMC and mode of action, see attachment K (DMC charta).

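### The DLT definition names grade IV only, so a fatal BIBF 1120-related reaction does not count as a DLT and does not stop dose escalation

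*Protocol*

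**What the plan says.** Section 5.4.2 of the protocol contains the only DLT definition: "A DLT is defined as every severe adverse reaction CTC grade IV with possible or definite relationship to the study drug BIBF1120". Toxicity is graded by CTCAE version 4.0 over the first 28-day cycle.

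The count then drives the dose:

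- **No DLT:** "In case of no dose limiting toxicity (DLT), the dose will be increased by one dose level".
- **One DLT:** "In case of one DLT, up to three further patients will be recruited into the same dose level".
- **More than one:** "If >1 DLT occurs in one dose level in up to six patients, this dose level will not be further evaluated". At dose level 1 this means stepping down to 100 mg once daily.
- **Phase II dose:** the highest level with at most one DLT in six patients, subject to DMC approval.

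Two groups of events are excluded. Complications of treatment-related cytopenia (febrile neutropenia, infection during neutropenia, bleeding from low platelets) are out at any grade, unless the DMC finds them unexpectedly frequent. Complications that the investigator attributes to leukemia progression are also out, and that list includes "death due to disease progression".

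On oversight, section 9.1 states: "During phase I, the DMC members will receive safety reports after completion of each dose level". After each report the DMC can recommend continuing, modifying or ending the study.

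**The concern.** The definition fixes one grade, with no sign for *or higher*. On the CTCAE scale death is grade V, so a fatal reaction related to BIBF 1120 falls outside the sentence. The gap does not depend on the grade number alone: the definition never mentions death, while the exclusion list presupposes that a death could be a DLT. The two parts of section 5.4.2 do not fit together.

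The phase I objective is safety and tolerability, and section 3.1.1 names more treatment-related deaths as the risk of adding BIBF 1120. The rule that moves patients to a higher dose should say plainly that such a death counts. As written, it scores the worst outcome below a grade IV reaction from which the patient recovers.

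**Working it through.** **Reading the text.** The protocol states no figure for the DLT rule (no target DLT rate, no operating characteristics), so there is none to reproduce.

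1. The definition in 5.4.2 names grade IV alone. Neither the German synopsis (12.1) nor any other section adds grade V or related death.
2. Among deaths, the exclusion list names only those due to progression. A fatal cytopenia complication is also excluded, through the cytopenia wording.
3. The bare grade is not a house style for a threshold. Section 5.4.4.3 uses *at least* signs for liver values, and 5.4.4.2 spells out grade 3 or 4.
4. DMC approval is attached to the phase II dose. For the steps between levels 1, 2 and 3, the protocol gives the DMC a report and the power to recommend. It does not make escalation wait for approval.

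**Consequence without any assumed rate.** Take three patients at dose level 1 or 2, no grade IV reaction, and related deaths outside the exclusions.

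| Related deaths | As written | If fatal reactions count |
|---|---|---|
| 0 | 0 DLT, escalate | 0 DLT, escalate |
| 1 | 0 DLT, escalate | 1 DLT, up to three more patients at this level |
| 2 | 0 DLT, escalate | 2 DLT, level closed |

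In the last row at dose level 1, the next dose is 150 mg twice daily as written, and 100 mg once daily if deaths count.

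**Illustration with assumed rates.** Let p be the probability that a patient has a DLT. In the 3+3 scheme a level is passed with 0 of 3, or with 1 of 3 followed by 0 of 3:

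P(escalate) = (1−p)³ + 3p(1−p)² × (1−p)³

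As written, p is the grade IV rate. If fatal reactions count, p is the grade IV rate plus the related-death rate, treating the two as separate patients. With an assumed 10% grade IV rate:

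| Assumed related-death rate | p if deaths count | P(escalate) if deaths count | P(escalate) as written | Gap |
|---|---|---|---|---|
| 0% | 0.10 | 0.729 + 0.243 × 0.729 = 0.906 | 0.906 | 0 |
| 2% | 0.12 | 0.681 + 0.279 × 0.681 = 0.871 | 0.906 | 0.035 |
| 5% | 0.15 | 0.614 + 0.325 × 0.614 = 0.814 | 0.906 | 0.092 |
| 10% | 0.20 | 0.512 + 0.384 × 0.512 = 0.709 | 0.906 | 0.20 |

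The phase II condition shifts in the same way. P(at most 1 DLT in 6) = (1−p)⁶ + 6p(1−p)⁵ is 0.886 at p = 0.10 and 0.655 at p = 0.20. That step, unlike escalation, stands behind DMC approval.

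**The case against.** The strongest reply is that this is a wording slip and would not survive contact with a real death. The progression exclusion shows that related deaths were meant to count, and a sensible investigator or DMC would count them. A non-exempt death reaches the Safety Desk within 24 hours (7.1.3, 7.2), and the coordinating investigator reviews every SAE for its effect on trial conduct (7.2). All phase I patients are monitored (9.3), the DMC sees a report after each level (9.1), and the trial can be ended for toxicity (6.6.2). The DMC charter (Attachment K) is not available here and may require approval before each escalation.

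The affected set is also narrow: a related death in cycle 1 that is neither a cytopenia complication nor progression, and that was not already recorded as grade IV. Nothing in the protocol supports a particular death rate, and treating fatal and grade IV events as separate gives the largest gap. With full overlap the gap is zero.

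Much of this stands. It limits the practical risk and makes the probabilities illustrative only. It does not repair the sentence. The safeguards report and review a death, but none scores it as a DLT. Section 5.4.2 lets the DMC turn frequent cytopenia complications into DLTs and says nothing similar for related deaths. A decision rule should not depend on readers inferring its threshold from its exclusions.

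**Conclusion.** The definition is wrong as written and should be corrected; the practical severity is modest. Applied literally, a related death outside the exclusions is not a DLT, and a cohort with one or even two such deaths and no grade IV reaction escalates. That conclusion needs no assumed rate. The size in probability terms does: from 0 to about 0.20 in the chance of escalating, for an assumed 10% grade IV rate and related-death rates from 0% to 10%, with no overlap between the two.

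The exposure is escalation between phase I levels. It is not an automatic carry-over to the 122 planned phase II patients, because DMC approval (5.4.2, 9.1) and a protocol amendment fixing the dose (5.4.3) come first.

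**What to change.** In section 5.4.2, define a DLT as an adverse reaction of *CTC grade IV or V (including death) with possible or definite relationship to BIBF 1120*. Leave the cytopenia and progression exclusions as they are. A fatal infection during neutropenia or a fatal bleed from low platelets then stays outside the count unless the DMC judges such events unexpectedly frequent, as now.

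The change is a few words in one sentence and needs no extra visits, data or staff. Its only cost is that escalation may stop earlier.

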### 5.4.3 Phase II – part

In the phase II part, patients will receive the treatment as described in 5.4.1 with the dose level of BIBF 1120 as defined in the phase I part of the study. Prior to the start of the phase II, the dose level as determined in the phase I part will be amended to the protocol. Responding patients after the therapy (CR, CRp, CRi) will be observed until one year after therapy initiation. During the observation period of responding patients, monthly visits with CBC with differential blood count and a bone marrow aspiration every 3 months and additionally in case of suspected relapse will be performed (for details, see 6.1). Patients with a partial remission or stable disease will continue in protocol treatment for up to six therapy cycles. In case of progressive disease or intolerable toxicity, study treatment will be terminated and the patient will be observed for survival until one year after start of therapy. However, timelines for AE and SAE reporting apply during the observation period (see 7.2).

### 5.4.4 Dose modification and delays

The dose modifications of BIBF 1120 will follow the following pre-defined dose levels:

|               |                    |
|---------------|--------------------|
| Dose level 3: | 200 mg twice daily |
| Dose level 2: | 150 mg twice daily |
| Dose level 1: | 100 mg twice daily |
| Dose level 0: | 100 mg once daily  |

#### 5.4.4.1 General dose modifications of BIBF1120

If a dose reduction below 100 mg once daily is required, the patient should be discontinued from the treatment with BIBF1120. After resolution of the adverse event the dose may be re-escalated at the discretion of the investigator. As a general rule, non-hematological grade 3 toxicity should be followed by permanent dose reduction of BIBF 1120. Resolution of an adverse event is defined as disappearance or reduction of the adverse event to < grade 3 toxicity. For patients with grade 2 or greater toxicities present at baseline resolution to at least baseline levels will apply. No dose reductions / dose delays are required for non-hematological toxicities which are controlled with an effective specific treatment (i.e. Nausea / Emesis).

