#### 5.4.4.2 Dose modifications for hematological toxicity of BIBF1120 and cytarabine.

For an effective antileukemic activity, a hematotoxicity is an unavoidable side effect of the combination therapy. Since only patients with persisting leukemia receive additional

chemotherapy / BIBF cycles, no routine dose modifications or dose delays are considered for hematological toxicity during the combination therapy. In case of grade 3 or 4 complications of hematotoxicity (thrombocytopenic bleeding, neutropenic infections, neutropenic fever) both cytarabine and BIBF1120 will be paused and will both be restarted without dose reduction upon improvement to grade 2 or lower. If, however, a continuation of the combination treatment places the patient to an inadequate risk in the opinion of the investigator, study treatment including treatment with cytarabine should be discontinued.

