#### 5.4.4.3 Dose modifications for non-hematological toxicity

The general recommendations for non-hematological toxicities are listed in table 1-2.

| Table 1-2: Non-hematological Criteria for Dose Delay and Dose Modification of BIBF 1120                                                                             |                                         |                                      |
|---------------------------------------------------------------------------------------------------------------------------------------------------------------------|-----------------------------------------|--------------------------------------|
| Grade                                                                                                                                                               | Dose Delay                              | Dose Modification                    |
| Grade 0-2                                                                                                                                                           | Treat on time                           | No Change                            |
| Grade 3                                                                                                                                                             | DELAY a until $\leq$ Grade 2 | DECREASE one dose level b |
| Grade 4                                                                                                                                                             | OFF protocol therapy                    | OFF protocol therapy                 |
| a. If no recovery after 30 days delay, treatment will be discontinued
b. If a dose reduction below 100 mg once daily is required, treatment will be discontinued |                                         |                                      |

These recommendations pertain, if the adverse event is considered to be related to BIBF 1120, but not to cytarabine.

BIBF 1120 must be interrupted in the event of AST and/or ALT elevations of CTCAE Grade 3 or 4 or AST and/or ALT elevations CTCAE grade  $\geq 2$  in conjunction with bilirubin elevation of CTCAE grade  $\geq 1$  and further treatment withheld until recovery of the abnormal laboratory parameters. After recovery, BIBF 1120 should only be reintroduced with a lower dose (decrease one dose level).

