## 7.2 Period of observation, documentation and reporting

All AEs, including SAEs, will be recorded from the time of signing the informed consent until 28 days after last protocol treatment including low-dose cytarabine. Medical judgment should be used to determine the relationship, considering all relevant factors, including pattern of reaction, temporal relationship, de-challenge or re-challenge, confounding factors such as concomitant medication, concomitant diseases and relevant history. Assessment of causal relationship must be recorded for each adverse event

All AEs, including SAEs, have to be recorded on the appropriate adverse event pages in the CRF.

Documentation and assessment by the investigator includes:

- Diagnosis or Description of AE
- Date of onset and date of end of AE
- Seriousness (yes/no)

- Severity, graded according to the National Cancer Institute Common Terminology Criteria for Adverse Events (CTCAE) v 4.0 for Cancer Clinical Trials
- Causality (reasonable possibility/no reasonable possibility)
- Action taken with investigational medicinal drug (none/dose changed/drug temporarily withdrawn/drug permanently withdrawn)
- Outcome (recovered/resolved, recovering/resolving, not recovered/not resolved, recovered/resolved with sequelae, fatal, unknown)

If possible, a diagnosis rather than a list of signs, symptoms and laboratory abnormalities should be given.

All AEs, including SAE, must be followed up until the condition resolves or stabilizes. (For definition of resolution of an adverse event please see 5.4.4.1.)

All SAEs identified by the protocol as requiring immediate reporting (for exceptions, see 7.1.3.2) and all AEs of special interest (for definition, see 7.1.3.1) must be reported on the SAE form in English and transmitted by fax to the Safety Desk within 24 hours of knowledge by the investigator. This applies regardless of severity (CTCAE v 4.0 grade) and whether or not the SAE is considered related to the use of study drug by the investigator. Personal data have to be replaced by the patient registration number before forwarding any information. SAEs requiring immediate reporting will be reported to Boehringer Ingelheim by the sponsor within the format and the timelines specified in the contract between sponsor and Boehringer Ingelheim.

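### Section 7.2 borrows a dosing threshold to end adverse event follow-up, so a grade 3–4 event that is down to grade 2 and still changing may be dropped

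*Protocol*

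**What the plan says.** Three pieces of the protocol act together.

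- **The duty to follow** (section 7.2): "All AEs, including SAE, must be followed up until the condition resolves or stabilizes".
- **The cross-reference** (section 7.2, directly after the duty): "For definition of resolution of an adverse event please see 5.4.4.1".
- **The definition** (section 5.4.4.1, on dose modification of BIBF 1120): "Resolution of an adverse event is defined as disappearance or reduction of the adverse event to < grade 3 toxicity". One qualification follows it: "For patients with grade 2 or greater toxicities present at baseline resolution to at least baseline levels will apply".

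Section 7.2 also sets the recording window: adverse events "will be recorded from the time of signing the informed consent until 28 days after last protocol treatment". Its list of outcome codes keeps recovered/resolved apart from recovering/resolving.

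**The concern.** In section 5.4.4.1 the definition answers a dosing question: when may the BIBF 1120 dose be raised again after toxicity? Falling below grade 3 is a reasonable answer. Section 7.2 asks something else: when may the investigator stop finding out what happened to the patient? With the same threshold for both, observation can end while the event is still present and still moving.

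The data at stake are the later course and true end date of improving grade 3–4 events, and any non-serious worsening more than 28 days after last treatment. Late worsening is mainly a phase II matter, because phase I patients are followed only until 28 days after the last study medication. The outcome data feed the phase I safety and tolerability evaluation (the primary endpoint of that part), the phase II toxicity evaluation (a secondary endpoint) and the safety reports to the data monitoring committee.

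**Working it through.** No power, alpha or rate enters this point, so the check is to set the rules side by side and apply them.

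**1. Is the definition a dosing rule?** Yes. It follows the sentence in 5.4.4.1 that allows re-escalation after an event has resolved. It matches the restart rule in 5.4.4.2, under which both drugs "will both be restarted without dose reduction upon improvement to grade 2 or lower" after a complication of hematotoxicity, and the grade 3 row of Table 1-2, which delays BIBF 1120 until grade 2 or lower.

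**2. Does meeting it end follow-up?** Yes. In 7.2 the two limbs are joined by *or*, and the first is defined by reference to 5.4.4.1. An event that meets that definition needs no further follow-up, whether or not it has stabilized.

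**3. What happens to typical events?** The last column uses disappearance, return to baseline or stabilization instead.

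| Baseline grade | Worst grade | Current grade | Present text | Return to baseline, or stable |
|---|---|---|---|---|
| 0 | 4 | 2, still changing | may stop | continue |
| 1 | 3 | 2, still changing | may stop | continue |
| 0 | 3 | 2, stable | may stop | may stop |
| 2 | 4 | 2 | may stop | may stop |
| 3 | 4 | 3 | may stop | may stop |

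The difference lies in the first two rows. Required follow-up may end 2 − 0 = 2 grades above a baseline of grade 0, or 2 − 1 = 1 grade above a baseline of grade 1. The baseline sentence does not reach these patients, because it applies only when toxicity of grade 2 or more was present at baseline.

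**4. Does another section set a stricter end point?** No. Sections 6.1.4 and 6.1.5 ask for the outcome of adverse events to be monitored, but both refer back to chapter 7. The SAE provisions in 7.2 set times for follow-up information and require queries to be answered; they do not say when follow-up of the event may end.

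**5. Would scheduled visits capture the rest anyway?** Only in part. Table 2 schedules blood counts and chemistry weekly within cycles. Chemistry is not scheduled in the observation, suspected-relapse or end-of-study columns; repeats there are left to the physician. Under Table 1-2, a grade 4 non-hematological event attributed to BIBF 1120 and not to cytarabine takes the patient off protocol therapy. After intolerable toxicity, a phase II patient is observed for survival and a phase I patient only until 28 days after the last medication. For these severe events, section 7.2 is the main rule requiring follow-up to an outcome.

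**6. Can affected events be counted?** No. That needs the grade 3–4 event rate for BIBF 1120 with low-dose cytarabine and the share of such events still changing at grade 2. The protocol gives neither. Section 5.4.2 calls neutropenic fever, neutropenic infection and thrombocytopenic bleeding frequent, but states no rate.

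**The case against.** The strongest reply is that the definition is correct where it stands, that only one parenthetical reference in 7.2 is open to question, and that its reach is narrow.

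- **Stabilization.** A stable grade 2 event may leave follow-up under the present text and under the proposed change. This stands, and it confines the point to events still changing.
- **Re-recording.** Worsening up to 28 days after last treatment is recordable as a new adverse event, and a later SAE suspected to be related may still be reported. Both stand. Late reporting is optional, however, and such events need not go on the CRF adverse event page.
- **The 28-day limit is a separate rule.** Correct: the cross-reference does not create it and the change would not move it. The change would only keep already open events open.
- **Phase I.** Dose finding uses toxicity in the first 28-day cycle, and grade, seriousness and causality are recorded regardless. The phase I loss is therefore mostly in outcome and end date.
- **Other safeguards.** For the liver enzyme elevations named in 5.4.4.3, BIBF 1120 is interrupted and "further treatment withheld until recovery of the abnormal laboratory parameters". The coordinating investigator reviews each SAE. These help, but they govern dosing and SAE assessment; they do not extend required follow-up of adverse events in general.
- **Coding.** An improving grade 2 event has a proper code, recovering/resolving, and the text does not direct miscoding. This stands. The definition nevertheless calls the same event resolved, which invites inconsistent coding and end dates.

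One could also argue that events never above grade 2 count as resolved from onset. That is not relied on here: the definition speaks of a reduction, which presupposes a fall from grade 3 or higher.

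**Conclusion.** The concern holds as a minor one. By explicit cross-reference, section 7.2 ends required follow-up at a dosing threshold, and no other section sets a stricter end point. A grade 3–4 event at grade 2 and still changing may leave follow-up as much as 2 grades above baseline.

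The conclusion rests on reading *resolves or stabilizes* as alternatives and the cross-reference as meaning what it says. Investigators may in practice follow events longer than the text requires. The effect is limited to adverse event follow-up and outcome data. Dose-limiting toxicities, the overall response rate and the sample size do not change, and no effect on any reported toxicity grade has been shown.

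**What to change.** - **Section 7.2:** delete the reference to 5.4.4.1. Define resolution, for follow-up purposes, as disappearance of the event or return to its baseline level. Keep stabilization as the alternative stopping point.
- **Section 5.4.4.1:** state that the below-grade-3 definition applies to dosing decisions only.
- **CRF completion note:** code events that have improved but persist as recovering/resolving.

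The cost is two sentences of amendment wording and the note. No scheduled visit or procedure is added. The downside is slightly longer follow-up of some events.
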